### Statistical methods

Data analysis will be performed according to the modified intention-to-treat population. Moreover, the per-protocol analysis will be used as a sensitivity analysis. We expect very few patients to be lost. As a result, the missing data will be minimized when analyzing primary outcomes. Multiple imputation will be used to handle missing data if needed.

Shapiro–Wilk test is used to test normality. Quantitative indicator is expressed as mean ± standard deviation or median (interquartile range, IQR), while qualitative data is expressed as median (interquartile, IQR). Quantitative indicators are tested by independent sample *t* test or Mann–Whitney *U* test according to data distribution. Qualitative data is tested by the chi-square test/Fisher’s exact test. Statistical analysis will be performed by SPSS 27.0.

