**Discussion:**

Our study is the first trial investigating whether maternal oxygen supplementation with HFNO can reduce the umbilical artery lactate levels and the incidence of fetal acidemia in cesarean section under combined spinal-epidural anesthesia.

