### Outcome assessment

The primary outcome is UA lactate levels. The secondary outcomes include UA pH, PO_2_, PCO_2_, BE, the incidence of pH < 7.20 and pH < 7.10, Apgar scores at 1 and 5 min, and the neonatal adverse outcomes in the operating room and ward (such as intubation, mechanical ventilation, and admission to neonatal unit). Others include the number of hypotensive episodes, the number of vasopressor boluses required, the incidence of tachycardia, bradycardia, arrhythmias, the time from subarachnoid injection to skin incision, the time of oxygen supplementation, and the time from skin incision to fetal delivery.

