Khaw et al. have concluded that hyperoxia may increase fetal oxidative stress and have a negative effect [6]. But the mean duration of oxygen administration was longer than 50 min. In another study by the same team, however, there were no differences in maternal or umbilical oxidative stress indices between the groups, and the mean oxygen exposure duration was 30 min [8]. Therefore, in our study, the duration of oxygen exposure is limited to the time between the completion of anesthesia placement and neonatal delivery. The time is usually 15–30 min in our center and rarely more than 40 min. In order to clarify the effect of hyperoxia on oxidative stress, malondialdehyde (MDA) of UA blood will also be measured.

In conclusion, for this research, we want to demonstrate whether supplemental oxygen with HFNO has a positive effect on fetal outcomes and decreases the incidence of fetal acidemia in in pregnant women who undergo elective cesarean section. The results of this research will be reported to peer-reviewed journals. Furthermore, we hope HFNO can be used for women with fetal distress to improve fetal outcomes, as an effective intrauterine resuscitation technique during emergency cesarean section.

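### The plan summarises categorical outcomes as median (IQR), which does not fit its own chi-square/Fisher tests and would usually print 0 (0–0) for yes/no secondary outcomes; they should be given as n (%)

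*Protocol article*

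**What the plan says.** In the protocol article, Statistical methods gives two summary rules. Quantitative measures are reported as mean ± SD or as median with IQR. For the other class, "qualitative data is expressed as median (interquartile, IQR". The same paragraph continues: "Qualitative data is tested by the chi-square test/Fisher’s exact test". It names no count or percentage.

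Outcome assessment states that "The primary outcome is UA lactate levels" and places "the incidence of pH < 7.20 and pH < 7.10" among the secondary outcomes, together with neonatal events such as intubation, mechanical ventilation and admission to the neonatal unit. Its list of other outcomes includes the incidence of tachycardia, bradycardia and arrhythmias.

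Two places put incidence alongside the main aim. The Discussion paragraph of the Abstract says the trial investigates whether HFNO "can reduce the umbilical artery lactate levels and the incidence of fetal acidemia in cesarean section". The closing paragraph of the main Discussion says "we want to demonstrate whether supplemental oxygen with HFNO has a positive effect on fetal outcomes and decreases the incidence of fetal acidemia". The sample size section works from UA lactate alone and states no rate of acidemia.

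**The concern.** A yes/no variable coded 0/1 has a median of 0 whenever fewer than half the patients have the event, and an upper quartile of 0 whenever fewer than about a quarter do. A median with IQR then hides the one quantity of interest, the proportion. The article states this as a rule, so the problem is an incorrect instruction and not a detail left to a fuller document.

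At stake is the readability of the binary outcomes. If the rule were applied as written, a table would show the same entry in both arms and the p value would carry all the information. That matters most for the pH thresholds, because the article raises incidence of acidemia twice as a question while the trial is sized for a continuous marker. With few events, a p value without counts or an interval is easily misread.

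**Working it through.** **1. What qualitative means here.** Chi-square and Fisher's exact tests take tables of counts, and the article assigns them to qualitative data. The term therefore means categorical data, and the summary and the test in the same paragraph do not match. Reading the sentence as meant for ordinal scores such as Apgar does not rescue it, because it covers all qualitative data.

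**2. When the summary collapses.** 120 patients at 1:1 give 60 per arm. Sort 60 values coded 0/1.
- With 14 events, the 45th and 46th values are both 0, so the upper quartile is 0 and the entry is 0 (0–0).
- With 15 events, the 46th value is 1 and the upper quartile rises above 0.
- The threshold is therefore 14/60 = 23%, or roughly a quarter of the arm.

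The probability that one arm prints 0 (0–0) is P(X ≤ 14) with X ~ Binomial(60, p). The rates are assumptions, since the article gives none.

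| Assumed true rate | P(arm prints 0 (0–0)) |
|---|---|
| 5% | above 99.9% |
| 10% | 99.9% |
| 15% | 97% |
| 20% | 79% |
| 30% | 16% |

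Example: 1/60 (1.7%) against 12/60 (20.0%) is a risk difference of 18.3 percentage points. The simple 95% interval is 0.183 ± 1.96 × √(0.2×0.8/60 + 0.0167×0.9833/60) = 7.7 to 29.0 points, with Fisher p = 0.002. The stated format would show 0 (0–0) in both arms.

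**3. What the sample size was built for.** The stated 53 reproduces as a per-arm figure for lactate. Take SD 0.028 (the bracketed figure, read as an SD) and a difference of 0.77 × 0.02 = 0.0154, which is inferred and not stated. The standardised difference is 0.0154/0.028 = 0.55.
- Normal approximation: 2 × (1.960 + 0.842)² / 0.55² = 51.9, so 52.
- Noncentral t: 52.87, so 53 per arm, with power 0.801.

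No incidence enters this calculation.

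**4. Power for incidence.** Two-sided Fisher's exact test at 0.05, power by enumerating all pairs of binomial counts. Control rates and effects are assumptions. The 51 per arm is 60 × 0.85, after the planned 15% loss.

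| Control rate | Halved, 60 per arm | Halved, 51 per arm | Reduced to zero, 60 per arm |
|---|---|---|---|
| 5% | 2% | 1% | 8% |
| 10% | 9% | 7% | 56% |
| 15% | 17% | 13% | 90% |
| 20% | 25% | 20% | 99% |
| 30% | 42% | 36% | above 99% |

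Against zero events in one arm, at least 6 of 60 are needed in the other: 5 v 0 gives p = 0.057 and 6 v 0 gives p = 0.027. If both arms share the rate, the 95% half-width for a risk difference is 1.96 × √(2p(1−p)/60), which is 7.8 points at 5% and 10.7 points at 10%.

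**The case against.** The strongest reply is that this is a display slip, almost certainly for n (%). The outcome is already named as an incidence, which is a proportion, and the tests are the right kind for counts. No test, decision or primary result depends on the sentence. That stands, and it keeps the point minor. It does not make the sentence correct, and the article is the published statement of the plan.

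A second reply is that a risk difference with interval is detail an article may leave to a fuller document. That also stands: its absence alone would be no finding. It is proposed here only because the sentence has to be rewritten anyway.

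The reply is also right about hypotension. Outcome assessment lists a number of hypotensive episodes, a count for which median with IQR is acceptable, so it does not belong among the affected outcomes.

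A reader might infer something stronger: that the article promises to show a fall in acidemia and that this trial cannot show one. The documents do not support that. Both the Abstract and the Discussion ask whether incidence falls, and the title only names the subject. The pH thresholds are declared secondary outcomes, which need not be powered. No acidemia rate is given, and elimination from an assumed 15% would be detected with 90% power. Nor do the documents support barring every statement on incidence; that would be a preference.

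**Conclusion.** The summary rule for qualitative data is wrong as written and contradicts the tests set for the same data. Taken literally, it empties the reported summary for any binary outcome that affects fewer than about 25% of an arm (14 or fewer of 60). That follows from the definition of the quartiles and needs no assumed rate; only how often it would happen does.

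On incidence of acidemia the supportable statement is limited. The trial is sized on UA lactate, and power for a moderate reduction is low: about 2% to 42% for a halving, at assumed control rates of 5% to 30% with 60 per arm. A very large reduction from a high control rate could still be detected. This is a reason to label the incidence statements as secondary or exploratory, not a design fault.

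The correction is minor. It concerns how the binary outcomes are reported and leaves the tests and the primary analysis as they are.

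**What to change.** In Statistical methods, replace the summary rule for qualitative data with: *Qualitative data are presented as n (%) per arm, with the risk difference and 95% CI; chi-square or Fisher's exact test.* The essential part is n (%); the risk difference with interval is a worthwhile addition. If Apgar scores are to keep a median with IQR, say so for them by name.

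Optionally, in the Discussion paragraph of the Abstract and the closing paragraph of the main Discussion, describe incidence of fetal acidemia as a secondary or exploratory question beside the primary outcome of UA lactate.

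The cost is one sentence and, if adopted, two short qualifiers. No further patients, data or change of test are needed.

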## Introduction

Maternal oxygen supplementation has been widely used for intrauterine resuscitation intervention in the clinic to prevent neonatal acidemia. Previous studies have reported that maternal hyperoxygenation has a positive effect on fetal heart rate pattern during the second stage of labor in the presence of suspected fetal distress [1], and is associated with a low overall rate of the composite neonatal adverse outcome [2].

However, fetal acidemia is more likely to occur during a cesarean section than during labor. The functional residual capacity and reserve oxygen capacity of pregnant women are decreased by uterine migration and obesity, and these changes are worsened in the supine position. Moreover, maternal oxygen consumption is increased by fetal and placental metabolism. In addition, spinal block-induced sympathicolysis decreases maternal systolic arterial blood pressure, causing hypoxia and anaerobic metabolism in infants [3]. Previous study suggests that the indication of cesarean section is also a risk factor of fetal acidemia [4].

Studies focused on the effect of maternal oxygen supplementation during cesarean section have shown mixed results. Prior researches demonstrated that maternal oxygen improved PaO_2_ in the umbilical artery (UA) [5–8]. A prospective trial observed higher UA pH values in the receiving oxygen group [9]. Moreover, a recent meta-analysis specifically assessing the use of supplemental oxygenation at the time of cesarean delivery concluded that oxygen supplementation was associated with lower rates of UA pH less than 7.2 [10]. But, several trials have shown that maternal oxygenation had no effect on UA pH [8, 11, 12] and fetal wellbeing [13].

In the previous trials, the concentrations and flow of oxygen inhalation were inconsistent. The maximum oxygen flow rate was not more than 10 L/min [7]. It has been demonstrated that providing 35% oxygen via a facemask does not significantly improve fetal oxygen delivery during cesarean section under spinal anesthesia [14]. But 60% supplementary oxygen increased fetal oxygenation [6, 8]. Therefore, the different concentrations and flows may have different effects.

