### Exclusion criteria

Participants will be excluded if they have any of the following conditions:Fetal or placental abnormalities are known(premature rupture of membranes, severe intrauterine distress, and fetal malformation)Maternal with complications (eclampsia or cardiovascular or cerebrovascular disease)Maternal BMI ≥ 40 kg/m.^2^Difficult intubation history or known difficult airwayContraindications for HFNO such as nasal lesions or structural changesGastroesophageal reflux disease

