### Sample size calculation

According to a retrospective observational study, there was a strong inverse correlation between lactate and pH (*r* =  − 0.77, *p* < 0.001) [18], and the clinically significant change of UA pH is assumed to be 0.02 pH units [19]. According to the experience of our hospital, the mean of the UA lactate is 2.0 (0.028) mmol/l. With a probability of *α* = 0.05, *β* = 0.2, and power of 0.80, the sample size was 53 according to a 2-side 2-sample equal-variance *t* test. Considering 15% patient loss, we are going to recruit 120 patients. The sample size was calculated with PASS software.

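### The unadjusted test planned for umbilical artery lactate is valid but may give away precision; a prespecified model with pre-allocation covariates would be a low-cost improvement

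*Protocol article*

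**What the plan says.** In the protocol article, Outcome assessment states that "The primary outcome is UA lactate levels". Statistical methods covers all quantitative outcomes with one rule: "Quantitative indicators are tested by independent sample" t test or Mann-Whitney U test, depending on the distribution. No covariate model appears anywhere in the article. Sample size calculation uses the same kind of test: "the sample size was 53 according to a 2-side 2-sample equal-variance" t test. Randomization and blinding describes a blocked 1:1 sequence, with the envelope opened on the day of surgery, and states no stratification factor.

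The Introduction says that "the indication of cesarean section is also a risk factor of fetal acidemia". On obesity it says only that functional residual capacity and "reserve oxygen capacity of pregnant women are decreased by uterine migration and obesity".

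BMI ("Maternal BMI ≥ 40 kg/m" is an exclusion) and gestational age (37 weeks or more is required) are eligibility items, and Table 1 schedules maternal information for the day before surgery. The first planned subgroup, under Data collection and management, is apparently parity, although its label is unclear.

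**The concern.** Neither the design nor the analysis uses any baseline information. Whatever share of the between-mother variation in UA lactate could be explained by BMI, gestational age or indication stays in the error term. A chance imbalance in a prognostic factor also stays in the estimate. This is separate from whether a normality test should choose between the t test and the Mann-Whitney test: a fixed t test would have the same feature.

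It matters somewhat more here because the trial is small and its allowance for loss is tight. If the planned 15% are lost, 120 recruited leaves 102, or 51 per arm, which is below the 53 that the calculation asks for. Adjustment can recover some precision without further patients, provided the covariates predict the outcome.

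**Working it through.** **Inputs.** From Sample size calculation: two-sided alpha 0.05, "and power of 0.80", n = 53 (read as per arm), lactate-pH correlation r = -0.77, a pH change of 0.02, and "the mean of the UA lactate is 2.0 (0.028) mmol/l", with 0.028 read as the SD. Loss is 15% and the total is 120. R-squared of the covariates for UA lactate is not given, so 0 to 0.20 is assumed.

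**Step 1: reproduce the plan's figure.** No lactate difference is stated. Taking 0.77 × 0.02 = 0.0154 as the difference gives d = 0.0154 / 0.028 = 0.55. For an equal-variance t test the noncentrality is d × √(n/2) = 0.55 × √26.5 = 2.83 on 104 degrees of freedom, and power is 80.1%. So 53 per arm is reproduced. Using 0.02 as the difference gives 32 per arm, and 0.02/0.77 gives 20, so neither matches.

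**Step 2: unadjusted power after the planned loss.** At n = 51 per arm the noncentrality is 0.55 × √25.5 = 2.777 on 100 degrees of freedom, and power is 78.5%.

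**Step 3: adjusted power.** With k covariates, the variance of the treatment estimate is multiplied by (1 - R²) × V. Here V = 1 + k/(2n - k - 3) is the expected cost of chance imbalance, and k degrees of freedom are lost. For k = 3 and n = 51, V = 1 + 3/96 = 1.031. The noncentrality becomes 2.777 / √((1 - R²) × V) on 97 degrees of freedom.

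| Assumed R² | (1 - R²) × V | Noncentrality | Power | Equivalent change in patients |
|---|---|---|---|---|
| 0 | 1.031 | 2.735 | 77.3% | -3% |
| 0.05 | 0.980 | 2.806 | 79.3% | +2% |
| 0.10 | 0.928 | 2.883 | 81.4% | +8% |
| 0.20 | 0.825 | 3.058 | 85.7% | +21% |

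The last column is 1 / ((1 - R²) × V) - 1 and does not depend on d.

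**Step 4: break-even.** (1 - R²) × 1.031 = 1 gives R² = 0.03. With four covariates V = 1 + 4/95 = 1.042, break-even is about 0.04, and power at R² = 0 is 76.8%.

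**Step 5: chance imbalance.** With 60 per arm the SD of a standardized baseline difference is √(2/60) = 0.183. A given continuous covariate therefore differs between arms by more than 0.25 SD in about 17% of such trials.

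**The case against.** The strongest reply is that nothing here is wrong. Under 1:1 randomization the unadjusted test is unbiased, its type I error already allows for chance imbalance, and it matches the test used for planning. A covariate model could also stand in an analysis plan that is not shown. The first part stands in full. The second stands only in part: the article does not leave the test open but names it, so an analysis plan with a model would depart from the article.

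The next objection is that the benefit is not demonstrated. This also stands. The documents give no R-squared, and there is no fetal baseline lactate to adjust for. Eligibility restricts the trial to elective, term deliveries with BMI below 40 and excludes several fetal and maternal complications, which narrows the range of the likely predictors. The gain could be nil or slightly negative.

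A reader might infer that the protocol itself names obesity as a risk factor for fetal acidemia, or calls BMI, gestational age and parity prognostic. The text does not support that. The Introduction ties obesity to maternal respiratory reserve, and only cesarean indication is called a risk factor. No section calls gestational age or parity prognostic, and parity is itself an inference from an unclear subgroup label. The case for BMI and gestational age is that they are at hand before allocation and plausible, not that the sponsor has declared them prognostic. Indication has the best support in the document, but the article does not say whether it is recorded.

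**Conclusion.** This is an efficiency gain worth taking, not a flaw in validity. The plan fixes an unadjusted comparison for its single primary outcome, states no stratification factor, and holds at least two maternal covariates before the envelope is opened.

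A reader might infer that precision is certainly being lost. The documents show only that it may be. On the stated assumptions (three covariates, d = 0.55, 51 per arm), adjustment changes power by between about -1 point (R-squared 0) and +7 points (R-squared 0.20), with about +3 points at 0.10.

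The power figures inherit a weakness of the sample size section. The implied difference of 0.0154 is a correlation multiplied by a pH change, set against an SD labelled in mmol/l, so d = 0.55 has no sound lactate scale. The figures serve to compare adjusted with unadjusted analysis under the sponsor's own implied effect. They are not an estimate of the trial's true power.

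**What to change.** Before unblinding, specify the primary analysis as one linear model of UA lactate on arm plus maternal BMI and gestational age. Add cesarean indication and parity where these are recorded before allocation. State in advance which covariates enter, how indication is grouped (few categories, since each costs a degree of freedom), and whether lactate is analysed on the original or the log scale. Report the adjusted difference with its 95% confidence interval as primary, and keep the unadjusted comparison as supportive. Adjust for nothing that arises after allocation, such as hypotension, duration of oxygen or incision-to-delivery time.

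The cost is a short change to the analysis text, with no new patients and no new data for BMI and gestational age. As a change to the primary analysis it would probably count as an important modification, which Study design says goes to the ethics committee. Trial status expected recruitment to end on 31 December 2023, so the change should be dated and shown to precede unblinding. The statistical downside with three covariates is about 3% variance inflation, or roughly one power point, if they predict nothing.

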### Safety consideration

Participants can withdraw at any time during the trial. We will keep strictly to the indications and contraindications to minimize the risk of adverse events (AEs) which might be caused by the high-flow nasal oxygen. In the process of clinical research, all AEs will be recorded form truthfully and in detail, including the clinical features, occurrence time, severity, duration, related treatment, and outcomes of AEs. When an AE occurs, it is associated with high-flow nasal oxygen, then we will stop using the device. The severe adverse events will be reported to the Clinical Research Ethics Committee as soon as possible. And we will be responsible for the subsequent treatment.

### Oversight and monitoring

An anesthesiologist, an obstetrician, and a nurse midwife were employed at the coordination center for this study. A statistician will guide the statistical analysis of the data obtained for this study. The data monitoring committee (DMC) consists of an anesthesiologist, an ethics expert, a statistician, and a clinical trial management expert. All team members are independent of the sponsor, and there are no conflicts of interest. The DMC will hold a monthly meeting to review research progress, check the integrity of the data, and monitor the occurrence of AEs.

### Data collection and management

There is one researcher to record all the data of the preoperative, intraoperative, and postoperative and collect the case report forms timely, completely, and correctly. And another researcher will check the data to ensure data accuracy and productivity level. All data are confidential all the time. The research records and data will be allocated an individual trial identification number. All the data will be stored in a secure database, and the names and other personal information of subjects will not be recorded. People who have permission from the corresponding author can access this database. Moreover, researchers can email the corresponding author to have access rights to enable international prospective meta-analyses.

We have no plan for interim analysis until the study is achieved. We plan to conduct a subgroup analysis to explore the effect of treatment according to the following pre-specified subgroup: (1) unparturient and transparturient; (2) intraoperative circulatory stabilization and intraoperative circulatory instabilities.

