### Randomization and blinding

Randomization will be conducted by a computer-generated blocked randomization sequence. All participants conforming to the inclusion criteria are randomly assigned to the HFNO group or the air group at a ratio of 1:1. And the random numbers are placed in opaque envelopes and arranged in serial numbers, which are kept by an anesthesia technician. On the day of surgery, the envelope will be opened by the anesthesia technician when the patients enter the room and the grouping result can be obtained. Others are unaware of the group information.

Unblinding will only be allowed when serious adverse effects occur. Participants will be distributed and assigned in numerical order. The outcome will be assented by assessors, and the data will be calculated by statisticians who will not participate in the treatment. All original records including informed consent and CRF together with related letters will be reserved for 10 years and then destroyed according to the hospital standards.

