### Intervention

Participants will be monitored with electrocardiograph (ECG), pulse oxygen saturation, and non-invasive blood pressure after entering the room. Heart rate (HR), systolic blood pressure, and diastolic blood pressure were recorded every minute in the supine position. A 22G intravenous cannula will be inserted in the dorsum of a hand. All the patients will receive an intravenous 500 ml of Ringer’s lactate solution.

Combined spinal-epidural anesthesia will be performed at the L2–3 or L3–4 with the patient in the right lateral position. The anesthesiologist determined the local anesthetic dose of ropivacaine (12–15 mg) according to the height of the parturient. After injection of the local anesthetic solution, a 19G terminal closed epidural catheter will be placed. At the same time, oxygen will be supplied to patients in the HFNO group. The flow rate of 40 L/min heated to 37℃ with humidity 100% oxygen concentration is delivered through the Optiflow high-flow nasal cannula system. And the patients of the air group receive the 2 L/min with air pattern through the same device.

The patient is immediately placed in the supine position once the anesthesia procedure is completed with a left lateral table tilt of 15°. The upper level of the sensory block will be assessed in the midline, using a pin to test for the absence of touch sensation.

HR and blood pressure will be recorded every minute following the injection of the spinal drug until the baby is delivered. The vasopressor bolus is administered as soon as the hypotension is occurred. If hypotension is not corrected after 1 min, then additional boluses will be administered every minute until hypotension is corrected (HR ≥ 75 bpm, 50 μg of phenylephrine boluses; HR < 75, 6 mg of ephedrine boluses).

Umbilical arterial and venous blood samples will be obtained for blood gas analysis from a segment of the umbilical cord double-clamped before the baby’s first breath.

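### The stable/unstable intraoperative circulation subgroup is observed after allocation and during treatment, so arm comparisons of lactate within it can be biased if HFNO alters circulation

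*Protocol article*

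**What the plan says.** The last paragraph of Data collection and management states: "We plan to conduct a subgroup analysis to explore the effect of treatment according to the following pre-specified subgroup". Two factors follow. The first has garbled wording but appears to be parity, which is fixed before randomisation. The second is "2) intraoperative circulatory stabilization and intraoperative circulatory instabilities". The article does not define instability, does not treat the two factors differently and does not restrict how the second may be interpreted.

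Four other sections bear on the second factor:

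- Randomization and blinding, on when allocation is revealed: "the envelope will be opened by the anesthesia technician when the patients enter the room".
- Intervention, on the start of the study gas, just after the spinal injection is described: "At the same time, oxygen will be supplied to patients in the HFNO group". On what is recorded from then on: "HR and blood pressure will be recorded every minute following the injection of the spinal drug until the baby is delivered".
- Outcome assessment: "The primary outcome is UA lactate levels". After the secondary outcomes it adds: "Others include the number of hypotensive episodes, the number of vasopressor boluses required, the incidence of tachycardia, bradycardia, arrhythmias".
- Introduction, on the link between maternal circulation and the fetus: "spinal block-induced sympathicolysis decreases maternal systolic arterial blood pressure, causing hypoxia and anaerobic metabolism in infants".

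**The concern.** A subgroup analysis of a treatment effect relies on randomisation having balanced the arms within each subgroup. That holds for a characteristic fixed before allocation. It need not hold for one that develops while the treatment is running.

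If HFNO makes some patients stable who would have been unstable on air, the unstable stratum contains a different mix of patients in each arm, and so does the stable stratum. By the protocol's own account maternal pressure affects fetal anaerobic metabolism, so the mix is likely to matter for lactate. A within-stratum difference could then reflect who ended up in the stratum rather than what the gas did. Holding stability fixed also removes from the within-stratum contrast any benefit or harm that HFNO has by changing circulation.

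At stake is the reading of one exploratory analysis that would carry the label of a pre-specified treatment-effect subgroup.

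**Working it through.** **Step 1: timing, from the protocol article.** Allocation is opened at room entry. The gas starts around the spinal injection. Heart rate and pressure are recorded each minute from that injection to delivery. The Discussion confines oxygen exposure to the period from completed anaesthesia to delivery. Circulation during surgery and before cord sampling is thus observed after allocation and during exposure. This is so under any definition of instability, because the factor is intraoperative.

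**Step 2: overlap with outcomes.** The further outcomes cover low-pressure episodes, vasopressor use and disturbances of rate or rhythm. These are the natural components of circulatory instability. The article does not make the link, so it is an inference.

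**Step 3: a yardstick.** The sample size section gives r = -0.77, a pH change of 0.02 and a lactate of 2.0 (0.028) mmol/l, and states no lactate difference. Taking 0.77 × 0.02 = 0.0154 as the difference and 0.028 as the SD, a two-sided t test at 5% with 80% power needs 52.9, hence 53 per group. This reproduces the stated 53. The implied effect is 0.0154 / 0.028 = 0.55 SD, which is inferred.

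**Step 4: illustration with no effect of HFNO on lactate.** All inputs here are assumptions. A latent susceptibility U has correlation 0.5 with lactate, and logit P(unstable) = 0.4 + shift × arm + U.

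| Instability, air to HFNO | False arm difference in lactate, each stratum | Overall comparison |
|---|---|---|
| 58% to 58% (shift 0) | about 0 | about 0 |
| 58% to 48% (shift -0.5) | about 0.04 SD | about 0 |
| 58% to 38% (shift -1) | about 0.09 SD | about 0 |

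The largest value is 0.09 / 0.55, about one sixth of the inferred design effect. The sign is the same in both strata: HFNO looks worse.

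**Step 5: a second model.** Let a patient be unstable when U exceeds a cut-off, with 50% unstable on air and p on HFNO, and let rho be the correlation of U with lactate. With φ the normal density and z(p) the cut-off:

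- unstable stratum: rho × [φ(z(p))/p - φ(0)/0.5]
- stable stratum: rho × [φ(0)/0.5 - φ(z(p))/(1 - p)]

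Here φ(0)/0.5 = 0.3989/0.5 = 0.798.

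- p = 0.4, φ = 0.3863: unstable rho × (0.966 - 0.798) = rho × 0.168; stable rho × (0.798 - 0.644) = rho × 0.154. For rho of 0.3 to 0.5 this gives about 0.05 to 0.08 SD.
- p = 0.3, φ = 0.3477: unstable rho × (1.159 - 0.798) = rho × 0.361; stable rho × (0.798 - 0.497) = rho × 0.301. This gives about 0.09 to 0.18 SD.

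In simulated trials of 120, type I error within a stratum stayed near 5% to 7% for p = 0.4. It reached about 6% to 10% for p = 0.3.

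**Step 6: against sampling noise.** Take 53 per arm and the 58% to 38% case. The unstable stratum has about 0.58 × 53 = 30.7 and 0.38 × 53 = 20.1 patients, so with unit SD the standard error is √(1/30.7 + 1/20.1) = 0.29 SD. The stable stratum has 22.3 and 32.9, giving 0.27 SD. Biases of 0.04 and 0.09 SD move a nominal 5% error rate to about 5.3% and 6.1%.

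**The case against.** The case for leaving the plan alone has real weight:

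- **Bias is conditional.** In both models it is zero unless HFNO changes stability. The article attributes the fall in pressure to the spinal block and nowhere says that oxygen alters maternal haemodynamics. This stands, so it would be too strong to say that the subgroup breaks the randomisation. Nor can the trial confirm that HFNO leaves stability alone. At 50% instability and 53 per arm, the 95% margin on the difference in rates is 1.96 × √(2 × 0.25/53) = 0.19, about the size of the larger shift assumed above.
- **The bias is modest next to chance.** Step 6 bears this out under moderate assumptions.
- **The analysis is exploratory.** The article's wording says so, and the primary comparison keeps every pathway of effect.
- **The outcome overlap is inferred.** A condensed article may leave the definition to the analysis plan. The timing argument needs no definition.

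A reader might also infer that this subgroup could manufacture a benefit confined to unstable, or to stable, patients. The calculations do not support that. The false difference has the same sign and similar size in both strata, and HFNO looks worse when it is assumed to reduce instability. Swapping the arm labels reverses the sign in both strata together. A benefit in one stratum only would need a different structure, and neither the documents nor this check provides one.

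**Conclusion.** The point holds in a limited form. The article fixes, as a factor for exploring the treatment effect, a variable that is observed only after allocation and during the intervention. Pre-specifying it does not cure that. If HFNO alters circulatory stability, the within-stratum comparisons of lactate can be biased, and they exclude whatever HFNO does through haemodynamics.

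The size is illustrative: about 0.04 to 0.09 SD in both strata under the first set of assumptions, up to 0.18 SD under the strongest values tried, and about zero if stability is unaffected. The instability rates and correlations are assumed. The 0.55 SD yardstick and the overlap with the listed haemodynamic events are inferred.

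The primary comparison of lactate is not affected. The change is worth making before analysis because it is nearly free.

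**What to change.** Remove circulatory stability from the treatment-effect subgroups. Alternatively, keep it only as a descriptive, non-randomised analysis, with a statement that no arm effect will be claimed from it. Report haemodynamic events by arm, as the outcome section already plans.

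If a circulatory subgroup is still wanted, define it from the heart rate or blood pressure taken after room entry and before the spinal injection. The Intervention section already has these recorded. This answers a different question: whether the effect depends on the patient's starting circulation, not on how she fared during surgery.

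The cost is one sentence in the protocol or analysis plan, with no new data and no extra patients. The downside is that one planned exploratory analysis loses its causal reading.
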